# Time schedule

November 2012: Enrolment of the first patients and initiation of investigations.

December 2015: Enrolment of the last patients and investigations.

January 2016: End of follow up and trial lock.

Spring 2016: Assessments and analysis of first data.

Summer 2016: Publication of results.

# Background information

Ascites is a frequent complication of cirrhosis, occurring in 50% of patients within 10 years of the diagnosis and associated with 50 % mortality in two years. If hepatorenal syndrome occurs, the mean survival is only a few months. Bacterial infections in patients with cirrhosis occur at admission or during hospitalization in app. 30 % of patients(1). High Child-Pugh Score, variceal bleeding and low ascetic fluid protein levels are associated with high risk of infection(2;3).

A bacterial infection is an important precipitating event for the development of renal failure and hepatorenal syndrome, hepatic encephalopathy and possibly also variceal bleeding. The infections are mainly triggered by gut bacterial translocation,the migration of microorganisms from the intestinal lumen to mesenteric lymph nodes or extra-intestinal sites. Some studies have shown derangements in the gut micro ecology of patients with liver cirrhosis, partly due to a decrease in small intestinal motility, which could cause small intestinal bacterial overgrowth(4;5). Combined with structural and functional alterations of the intestinal mucosa and deficiencies in defence mechanisms, this bacterial overgrowth contributes to bacterial translocation.

Circulating bacterial DNA is a marker of bacterial translocation that may enhance endothelial dysfunction and predict a poor outcome in cirrhosis and ascites(6;7). Selective gut decontamination prevents spontaneous bacterial infections and improves survival in advanced cirrhosis, such as in variceal bleeding and in patients with spontaneous bacterial peritonitis (SBP)(8).

In bacterial infections due to translocation, endotoxines display their effect via TNFa-signalling and toll-like-receptor 4 (TLR4), which leads to an inflammatory response.(9-11)

This induces increased expression and activation of inducible NOS leading to excessive NO production and further vasodilatation. Patients with advanced cirrhosis are, apart from having portal hypertension, characterized by a marked systemic vasodilatation, an increased cardiac output and a low central blood volume. This could be due to raised levels of endotoxines in the blood. Furthermore, lipopolysaccharide-binding-protein (LBP), a surrogate marker of endotoxemia, as well as high levels of IL-6 and TNF-(12;13), is associated with a lower systemic vascular resistance (SVR) and a higher cardiac output (CO) in cirrhotic patients(14;15).

In decompensated cirrhosis several vasoactive hormones are activated to counterbalance the vasodilatation.

In animal studies, it has been shown that oral antibiotics might reduce bacterial translocation and the vasodilation in the splanchnic vasculature.(16-19)

Quinolones are widely used for this purpose, yet they carry a high risk of developing bacterial resistence and risk of clostridium difficile infections[8](#_ENREF_8). Rifaximin seems to be an attractive alternative that exerts a broad-range of antimicrobial activity including gram-positive bacteria. Rifaximin induces less bacterial resistance and acts predominantly in the small intestine, the site of bacterial overgrowth in cirrhosis(20).

Rifaximin has been shown to reduce the risk of hepatic encephalopathy(21;22), with less side effects than traditional lactulose treatment(23). One study has implied that rifaximin might have an effect on minimal hepatic encephalopathy (24). However, evidence of the mental effect of rifaximin on covert hepatic encephalopathy is still scarce.

The hepatic venous pressure gradient (HVPG) is a marker of severity of cirrhosis and has important prognostic value in the assessment of risk of complications to cirrhosis. An uncontrolled study has suggested that rifaximin may decrease HVPG(8). A recently published pilot study has furthermore suggested, that rifaximin might improve systemic hemodynamics by decreasing cardiac output and also increasing glomerular filtration rate (GFR)(25).

The overall idea of this trial is to assess the impact of rifaximin on the flow of events as described in the figure below, by blocking the second hit bacterial overgrowth and translocation and thereby improving splanchnic and systemic haemodynamics.

This novel, investigational trial will be assessing the effect of rifaximin on pathophysiology and haemodynamics in the patient with liver cirrhosis, and addressing several organs on marker level.

We will explore the molecular and physiological effects of rifaximin rather than confirming evidence of its already known beneficial effects.

[figure not shown]

# Aim and hypothesis

We hypothesize that intestinal decontamination with rifaximin in patients with cirrhosis and ascites will interrupt the progression of the disease from the first to the second hit as described in the figure. Based on these assumptions, we hypothesize, that rifaximin may have the following effects:

1. Will decrease portal pressure, measured as the hepatic venous pressure gradient (HVPG).
2. Will ameliorate the peripheral and splanchnic vasodilatation by a decrease in cardiac output (CO) and an increase in arterial blood pressure and systemic vascular resistance (SVR). These effects should also be reflected by a trend towards normalisation of vasoactive hormones.
3. Will improve renal function expressed as an increase in glomerular filtration rate.
4. Will downregulate markers of inflammation expressed as a decrease in proinflammatory cytokines (i.e. TNF- and interleukines) and high sensitivity CRP.
5. Attenuate markers of infection, expressed by bacterial DNA and lipopolysaccharide binding protein (LPS-BP).

## Outcome measures

The aim of this trial is mainly explorative and investigational and we aim to address a series of haemodynamic and biochemical parameters as to assess the effect of rifaximin comprehensively. Hence, we have included a range of outcome measures that will be addressed individually and in general.

## Primary outcome measures

Hepatic venous pressure gradient (HVPG), measured as the gradient between wedged and free hepatic venous pressure.

Glomerular Filtration Rate (GFR) assessed by chrome-EDTA clearance

## Secondary outcome measures

Cardiac Output (CO), assessed by indicator dilution technique.

Systemic vascular resistance (SVR) measured as dynxsxcm-5,

Mean arterial blood pressure (MAP) measured as mmHg,

Heart Rate (P) measured as beats/minute,

Biochemical markers of bacterial translocation and proinflammatory cytokines,

Effect on vasoactive hormones

Improvement in minimal Hepatic encephalopathy

Effect on weight and need of diuretics

Hospitalization during the treatment period,

Infections during the treatment period

Mortality and co morbidity during a follow-up period of 6 months.

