## Exclusion criteria

- Child-Pugh Score above 13
- Clinical signs of infection evaluated by blood biochemistry, urine culture and if applicable ascites puncture, and through clinical assessment by the investigator.
- Received antibiotic treatment within 14 days prior to inclusion
- Presence of hepatocellular carcinoma
- Ongoing invasive cancer or invasive cancer within the last five years,
- Overt hepatic encephalopathy (HE above grade 1),
- Serum creatinine > 200 mol/l,
- Transfusion requiring bleeding within one week prior to inclusion,
- Severe cardiac, pulmonary or kidney diseases or Type 1 diabetes mellitus,
- Continuous alcohol abuse with symptoms of abstinences
- Expected survival less than 3 months,
- Denied consent
- Plasma haemoglobin of less than 5,5 mmol/L

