## Withdrawal of trial participants

Trial participants are withdrawn from the study if they:

- Are in need of other antibiotics during study period,
- Are admitted to hospital for other morbidity and require treatment that is incompatible with continuous rifaximin treatment.
- If blinding is repealed.
- Experience deterioration in hepatic encephalopathy above grade 1 or develops hepatic encephalopathy, which will prevent further participation in the trial.

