# Measurements and investigations

The following flow-chart for the trial is applied. An extensive list of investigations and blood samples are given in appendix 6.

All scheduled investigations in this trial are standard procedures at the department of clinical physiology and nuclear medicine, Hvidovre Hospital. As well as blood analyses are standard procedures at the department of clinical biochemistry, Hvidovre hospital.

Standard Operating Procedures for all included investigations are therefore available to study nurses, investigators and other personnel participating in the survey and treatment of participants on the intranet for Hvidovre Hospital(26).

## Investigations on day 0

- The trial participant is fasting at admission to the hospital.
- Glucose breath test is performed to assess bacterial overgrowth.
- Hospitalisation and registration of the trial participant.
- Clinical examination by investigator or sub investigator and registration of clinical signs symptoms and basic values, That is height, weight, blood pressure, pulse, temperature.
- Routine blood samples for evaluation of kidney and liver function and possible infection (specified in appendix 6)
- To exclude occult infection: Blood culture and urinary culture.
- All women of childbearing age will have taken urine-HCG to exclude pregnancy.
- Diagnostic ascites puncture to exclude bacterial peritonitis, in case the patient has clinical ascites.
- Samples of faeces to assess bacterial composition in the gut.
- Examination of continuous reaction time (CRT) to assess possible minimal hepatic encephalopathy.
- Psychometric Hepatic Encephalopathy Score (PSE score)

All of the above blood analyses are done on peripheral blood, in total 65 ml of blood, and can be withdrawn from the same puncture site, except blood culture.

## Investigations on day 1

- The participant is fasting from the morning.
- DEXA scan is performed to determine body composition of fat, fat free mass and bone mineral composition.
- Liver vein catheterisation is performed including measurements of splanchnic haemodynamics and metabolism and systemic haemodynamics (analyses specified in appendix 6).
- Blood samples are drawn during catheterisation.
- Assessment of renal function (Cr-51-EDTA-clearance for determination of glomerular filtration rate, GFR)
- Measurements of biomarkers of renal function (specified in appendix 6)

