## Investigations on day 29-32

- At the end of the trial period, patients are re-hospitalized
- Programs of day 0 and day 1 are repeated, elaborated in appendix 6.
- Blood culture and urine culture are avoided if the participants show no signs of infection.
- A three-day treatment window is allowed to avoid admission of patients during weekends and holidays.

All blood analyses are done on liver vein blood, arterial or peripheral blood as specified above, in total 165 ml.

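### The minimal encephalopathy outcome is worded only as improvement in a condition that participants need not have at entry; it should be an effect on CRT and PSE score in all participants, compared between arms

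*Protocol*

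**What the plan says.** The list under Secondary outcome measures includes "Improvement in minimal Hepatic encephalopathy". It attaches no instrument, cut-off or analysis set to that line. A neighbouring line is neutral in direction: "Effect on weight and need of diuretics".

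None of the four inclusion criteria mentions encephalopathy. Under Exclusion criteria the only limit is an upper one: "Overt hepatic encephalopathy (HE above grade 1" (the closing bracket follows in the text).

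The day 0 programme, under Measurements and investigations, has two relevant tests for each participant: "Examination of continuous reaction time (CRT) to assess possible minimal hepatic encephalopathy" and "Psychometric Hepatic Encephalopathy Score (PSE score" (again with its closing bracket). At the end of treatment, "Programs of day 0 and day 1 are repeated, elaborated in appendix 6", so both tests are scheduled twice in everyone who completes.

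The Background gives the reason for interest: "evidence of the mental effect of rifaximin on covert hepatic encephalopathy is still scarce".

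The Statistics section states a general approach for all data: paired analysis of change, independent comparison between groups, and use of all available patient data.

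**The concern.** The outcome names a favourable change in a diagnosis, and only people who have the diagnosis can show that change. Participants may enter with anything from normal tests to grade 1 encephalopathy. Taken at its word, the outcome leaves out every test-normal participant. It also leaves out movement in the unfavourable direction, from normal on day 0 to abnormal on day 29-32. If rifaximin prevents minimal impairment, or if impairment appears more often in one arm, this outcome would not show it, although the tests would have recorded it.

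A second issue concerns the analysis. Psychometric tests repeated after four weeks tend to be done better the second time. If attention is confined to people who were abnormal on day 0, regression to the mean adds to the apparent gain. A paired test within the rifaximin arm cannot separate either from a drug effect. The protocol says that it expects no change under placebo on any outcome, which makes a within-arm gain easy to over-read.

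At stake is whether the trial's contribution on covert encephalopathy comes from a subset of unknown size and in one direction, or from all the scores collected.

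**Working it through.** The protocol gives no power, prevalence or improvement rate for this outcome, so there is no stated figure to reproduce. The check is a comparison of sections, then simple arithmetic over an assumed range.

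**Who can contribute under the literal wording**

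| Day 0 status | Allowed at entry? | Can improve? | Change for the worse counted in this outcome? |
|---|---|---|---|
| Normal on CRT and PSE | Yes | No | No |
| Minimal encephalopathy | Yes | Yes | No |
| Overt, above grade 1 | No | – | – |

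**How many that is**

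Inputs:
- Planned analysed sample: 32 rifaximin + 16 placebo = 48 (Statistics).
- Prevalence *p* of minimal encephalopathy on day 0: **not in the protocol**. It is assumed here at 30%, 50% and 70% to show the range.

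Number able to improve = 48 × *p*. Number unable to improve = 48 × (1 − *p*).

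| Assumed *p* | Able: rifaximin (32*p*) | Able: placebo (16*p*) | Able: total | Unable: total |
|---|---|---|---|---|
| 30% | 9.6 | 4.8 | 14.4 | 33.6 (about 34) |
| 50% | 16 | 8 | 24 | 24 |
| 70% | 22.4 | 11.2 | 33.6 | 14.4 (about 14) |

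The participants unable to improve are a majority only if 1 − *p* > 0.5, that is, if *p* is below 50%.

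**What the paired test measures**

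Write the expected change in score within an arm as

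- rifaximin arm: drug effect + practice + regression to the mean
- placebo arm: practice + regression to the mean

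Regression to the mean matters where the analysis is restricted to those abnormal on day 0; practice applies to anyone retested. The paired test in the rifaximin arm tests the whole first sum against zero. The difference between arms is, in expectation, the drug effect alone, because randomised arms tested on the same schedule share the other two terms. Only the between-arm comparison answers the question.

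**Whether worsening is captured elsewhere**

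- Withdrawal of trial participants lists those who "Experience deterioration in hepatic encephalopathy above grade 1 or develops hepatic encephalopathy, which will prevent further participation in the trial". This concerns encephalopathy above grade 1 or encephalopathy that prevents participation, not new minimal impairment. It may also remove the worst cases before the repeat tests.
- Follow up collects hepatic encephalopathy from medical records as a complication of cirrhosis. That would not be expected to show impairment found only by CRT or PSE score.

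**The case against.** The strongest reply is that the outcome line is a label and not a definition. The protocol nowhere sets up a responder count. Its hypotheses are directional too, for instance that portal pressure will fall, yet HVPG and GFR are plainly analysed as measured values. The Statistics section plans changes and group differences using all available data, which is compatible with analysing CRT and PSE change in everyone. Cut-offs, the leading instrument and the analysis set are commonly left to a statistical analysis plan, which is not shown. Practice affects both arms, and there is a placebo arm.

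Much of this stands:

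- A reader might infer that the plan tallies improvers and nothing else. The text does not say so, and the Statistics section points the other way.
- A reader might infer that most CRT and PSE data are lost. That needs a baseline prevalence below 50%, and the protocol gives none. The population has decompensated cirrhosis with grade 1 encephalopathy allowed, so a higher prevalence cannot be ruled out from the text.
- A reader might want a power figure for a responder comparison. It would rest on assumed rates and mainly reflect the trial's size, and the protocol claims no power for any secondary outcome.
- Not naming a leading instrument is not a fault of this document.
- Worsening is not wholly unrecorded: encephalopathy above grade 1 leads to withdrawal, with reasons for dropout sought, and clinical encephalopathy is in the follow-up.

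The wording itself is not answered. The outcome is stated in one direction, for a condition not required at entry, and nothing in the protocol says that the general analysis text overrides it. The placebo arm deals with practice only in the between-arm analysis; the paired analysis remains planned beside it with no statement of which one carries the conclusion.

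**Conclusion.** The point holds as one of wording and interpretation. Under its literal wording the outcome gives test-normal participants no way to contribute and does not count newly developed minimal impairment. The number affected is not known from the protocol: about 34, 24 or 14 of 48 at assumed prevalences of 30%, 50% and 70%. These figures take the planned 48 as analysed and the literal reading as the one applied. Separately, the planned within-arm testing should not be taken as evidence of effect for these repeated tests; that conclusion needs no numerical assumption.

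The importance is minor. This is one of eleven secondary outcomes in a trial that describes itself as mainly explorative, and the general analysis text already leaves room for the better analysis.

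**What to change.** Reword the outcome along these lines: *effect on minimal hepatic encephalopathy, measured as change in CRT and in PSE score from day 0 to day 29-32*. Then state that:

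- the two arms are compared in all participants with both measurements, adjusted for the day 0 score;
- resolved and newly developed minimal encephalopathy are reported side by side, by arm, as supportive counts;
- the within-arm change is descriptive only.

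Participants withdrawn before the repeat tests will be missing from the score comparison, so their number by arm, with the reasons already to be registered, should be shown next to it.

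The cost is a change of text: no added test, visit or participant, since both tests are already scheduled at both time points. The small downside is that a change in score is less directly clinical than a resolved diagnosis, which is why the counts are kept as support.

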## Follow up

A register based follow up on patients through medical records will be performed at the end of trial, which is 1 month after last patient’s last visit. Data collection will be limited to hospital admissions and reasons hereto, complications to liver cirrhosis (esophageal bleeding, spontaneous bacterial peritonitis, hepatic encephalopathy and hepatorenal syndrome), and mortality and reasons hereto.

Hence, patients will be followed up until death, or end of trial.

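### The six-month mortality and comorbidity outcome asks for longer follow-up than the protocol gives to the last patients enrolled

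*Protocol*

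**What the plan says.** Three sections of the protocol bear on this.

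- **Secondary outcome measures** ends its list with "Mortality and co morbidity during a follow-up period of 6 months". It does not say whether the six months start at day 0, at randomisation or at the last visit.
- **Follow up** describes a single register-based review, which "will be performed at the end of trial, which is 1 month after last patient’s last visit". It closes observation with "Hence, patients will be followed up until death, or end of trial". On content, "Data collection will be limited to hospital admissions and reasons hereto, complications to liver cirrhosis", and deaths with their causes.
- **Time schedule** opens with "November 2012: Enrolment of the first patients and initiation of investigations", places the last enrolments in December 2015, and then gives "January 2016: End of follow up and trial lock".

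No section gives each patient a six-month window or says how patients with less than six months are to be treated.

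**The concern.** A six-month outcome needs six months of observation per patient, or an explicit rule for those who have less. The protocol provides neither. A review tied to the last patient's last visit gives late enrolees a short period and early enrolees a long one. What is collected is follow-up to a common calendar date, which is a different quantity from events within six months.

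This goes beyond a detail for the statistical analysis plan. That plan can choose an estimator, but it cannot supply observation time that the protocol has cut off. Left alone, the named outcome will be missing part of its window for some patients, and for the others it will be unclear whether events after six months belong to it.

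**Working it through.** **Inputs (all from the protocol)**

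| Item | Value | Section |
|---|---|---|
| Outcome period | 6 months, start not stated | Secondary outcome measures |
| Last visit | day 29–32 | Investigations on day 29-32 |
| End of trial | last visit + 1 month | Follow up |
| Enrolment | November 2012 to December 2015 | Time schedule |
| End of follow-up | January 2016 | Time schedule |
| Planned enrolment | 38 + 19 = 57 | Statistics |

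**Step 1. Last patient under the one-month rule.** End of follow-up = day 0 + 29 to 32 days + 1 month.

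| Day 0 | Last visit | End of trial | Days from day 0 |
|---|---|---|---|
| 1 Dec 2015 | 30 Dec (day 29) | 30 Jan 2016 | 60 |
| 1 Dec 2015 | 2 Jan (day 32) | 2 Feb 2016 | 63 |
| 31 Dec 2015 | 29 Jan (day 29) | 29 Feb 2016 | 60 |
| 31 Dec 2015 | 1 Feb (day 32) | 1 Mar 2016 | 61 |

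The last patient has 60–63 days, about two months.

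**Step 2. Last patient under the January 2016 date.** Taking 31 January, the latest possible day: entry on 1 December gives 61 days and entry on 31 December gives 31 days. No variant comes near six months.

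**Step 3. Do the two end dates agree?** One month after the last visit falls in January 2016 only if that visit is no later than 31 December 2015. A day-29 visit by then needs entry by 2 December; a day-32 visit needs entry by 29 November. For later December entry the one-month rule ends in February or on 1 March, after the stated lock.

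**Step 4. Share of patients affected.** The protocol gives no accrual curve, so I assume even accrual from 1 November 2012.

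Share = (last entry − latest entry that still allows six months) ÷ (last entry − 1 November 2012).

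With last entry on 31 December 2015 the denominator is 1155 days.

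| Six months from | Follow-up ends | Entry needed by | Share | Of 57 |
|---|---|---|---|---|
| Day 0 | 1 Mar 2016 (one-month rule) | 1 Sep 2015 | 121/1155 = 10.5% | 6.0 |
| Day 0 | 31 Jan 2016 | 31 Jul 2015 | 153/1155 = 13.2% | 7.6 |
| Day 0 | 1 Jan 2016 | 1 Jul 2015 | 183/1155 = 15.8% | 9.0 |
| Last visit | 29 Feb or 1 Mar 2016 (one-month rule) | 31 Jul 2015 | 153/1155 = 13.2% | 7.6 |
| Last visit (day 32) | 1 Jan 2016 | 30 May 2015 | 215/1155 = 18.6% | 10.6 |

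Last entry on 1 December instead (denominator 1125 days) gives shares inside these ranges. Rounded, 11–16% (6–9 patients) fall short from day 0 and 13–19% (8–11 patients) from the last visit. The remaining 81–89% do reach six months.

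**Step 5. Spread of follow-up.** A patient entered on 1 November 2012 and followed to January 2016 has 38–39 months, against one to two months for the last. To illustrate what that means, Background information cites 50% mortality in two years with ascites. Under a constant hazard (an assumption), mortality by month t is 1 − 0.5^(t/24): about 6% at 2 months, 16% at 6 months and 67% at 38 months.

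**Step 6. Date needed.** Six months after the last day 0 (1–31 December 2015) is 1–30 June 2016. Six months after the last day 29–32 visit is 30 June to 1 August 2016.

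**The case against.** The best defence is that little is lost. Most patients complete six months under either starting point, and the others are cut off by calendar date rather than by prognosis. A censored analysis can estimate a six-month risk from such data, and the Follow up section already describes observation until death or end of trial. This is one of eleven secondary items in a trial that calls itself mainly exploratory, and neither primary outcome depends on it. All of this stands, and it limits the weight of the point. It does not remove the mismatch, because the outcome is still worded as a fixed six-month period and no censored analysis is stated.

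Three stronger readings are tempting, and the protocol does not support them:

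- **A reader might infer that the outcome cannot be delivered at all.** It is incomplete for a minority. Only a crude six-month proportion over all randomised patients is out of reach.
- **A reader might infer that crude event counts will be compared by arm, with bias from unequal exposure.** No section says crude counts will be used, and randomisation makes follow-up length similar between arms in expectation. The cost shown is in completeness and interpretation.
- **A reader might infer that the one-month rule always overruns the January lock.** It does not if the last patient enters in the first days of December. The Time schedule entry for December 2015 also mentions investigations. If that means the last visits fall in December too, the two end dates agree. Even then the last patient has only about two months.

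**Conclusion.** The point holds as an internal inconsistency. The six-month outcome, the one-month end-of-trial rule and the January 2016 end of follow-up cannot all stand for late enrolees. That the last patient falls short rests only on the protocol's own dates. The size, 6–9 of 57 from day 0 or 8–11 of 57 from the last visit, rests on even accrual; back-loaded recruitment would raise it and front-loaded recruitment would lower it. The upper ends take 1 January 2016 as the end of follow-up, the earliest reading of that entry. The disagreement between Time schedule and Follow up is conditional: it arises unless the last patient enters at the very start of December 2015. The HVPG and GFR analyses and their power are unaffected. The point should be corrected, but it does not threaten the trial's main result.

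**What to change.** 1. State in Secondary outcome measures when the six months begin.
2. Take the register review of deaths, admissions and cirrhosis complications no earlier than six months after that point for the last patient: June 2016 if counted from day 0, about July 2016 if from the last visit.
3. Count events in the same six-month window for every randomised patient whose consent and data remain available. The dropout sections allow for withdrawn consent and erased data, and plan no active follow-up of dropouts, so say which dropout data the review will use.
4. The haemodynamic data may still be locked and analysed early in 2016. If they are unblinded first, whoever classifies reasons for admission and death should stay blinded to treatment.
5. If the date cannot move, restate the outcome as time to event censored at end of trial, with the six-month risk estimated under that censoring.
6. Align Time schedule, Secondary outcome measures and Follow up.

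The cost is one later register review without patient contact, plus the blinding safeguard. This result would report about five to six months later, so the summer 2016 publication in the Time schedule would have to wait for it or appear without it. The censored alternative needs no extra time, but the latest patients then contribute only one to two months each.
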